#### 7.1.3.3. Observation Period

On Days 1, 15, and 28 of the observation period, the following will be performed

- Body Weight
- ECOG PS
- Hematology
- Blood Biochemistry Test
- Urinalysis
- Pregnancy test (for women with childbearing potential only, on Day 28)
- Chest X-ray
- Adverse event evaluation
- Contrast-enhanced CT (or contrast-enhanced MRI) scan (tumor evaluation, on Day 15)
- Anti-HLA antibody test (only on Day 1)
- Immune cell repertoire analysis (only on Day 1)

#### 7.1.3.4. Study Discontinuation

Within 7 days of the decision by the PI or SI to discontinue the study, the following will be performed as possible. However, if post-treatment is to be initiated, the following must be performed prior to the start of post-treatment.

- Body Weight
- ECOG PS
- Hematology
- Blood Biochemistry Test
- Urinalysis
- Pregnancy test (for women with childbearing potential only)
- Chest X-ray
- Adverse event evaluation
- Contrast-enhanced CT (or contrast-enhanced MRI) scan (tumor evaluation)
- Anti-HLA antibody test

#### 7.1.3.5. Tumor Evaluation

As a secondary endpoint, imaging studies will be performed to determine the efficacy of combination use of DC/Gal and iPS-NKT cells on the tumor.

At screening period, contrast-enhanced CT (or contrast-enhanced MRI) will be performed to detect the presence of evaluable tumor from the head and neck to the pelvic region.

After the start of iPS-NKT cell administration, target lesions from the head and neck to the pelvic region will be confirmed by imaging examination on the first day of the observation period (28 days after iPS-NKT cell administration or 15 days after the decision to discontinue administration, whichever comes later) and at the time of discontinuation. Even in subjects with no target lesions in the brain or extremities at screening period, the presence or absence of brain or bone metastases will be evaluated by imaging tests according to clinical symptoms.

Contrast-enhanced CT (or contrast-enhanced MRI) performed in this study will be performed in the same modality setting as much as possible for evaluation over time.

Efficacy evaluation will be performed according to the RECIST 1.1 Japanese translation of the JCOG version (see Appendix 1). When imaging for efficacy evaluation is performed, the PI or SI should promptly perform the evaluation and record the evaluation results.

#### 7.1.3.6. Pregnancy Outcome Study

If a female subject or male subject's partner is found to be pregnant during the study period, she will be followed until the outcome of the pregnancy is known, regardless of the study period.

#### 7.1.3.7. Follow-up after study completion

After the completion of the study, the subjects will be treated in the standard clinical practice.

### 8. Handling of Adverse Events, Quality Defects, etc.

#### 8.1. Definition of Adverse Event and Quality Defect

Adverse events are any unwanted or unintended symptoms (including abnormal changes in laboratory values) or illnesses that occur after DC/Gal or iPS-NKT cells have been administered, regardless of causal relationship to DC/Gal or iPS-NKT cells.

Preexisting conditions (complications that existed prior to the study period) will not be categorized as adverse events unless they worsen or increase in frequency during the study period. However, if a complication worsens after the administration of DC/Gal or iPS-NKT cells, it shall be categorized as an adverse event, and the date when the worsening is confirmed shall be recorded as the date of occurrence of the adverse event.

Quality defect refers to the failure of the function of the test product, etc., or adverse effects of the cells on the human body, or any other widely unfavorable conditions, regardless of whether the failure is due to the product itself, delivery, storage, or use of the product.

#### 8.2. Definition of Disease, etc.

Disease, etc. means any disease, disability, or death or outbreak of infectious disease that is suspected to be caused by the provision of regenerative medicine, etc. (hereinafter referred to as "occurrence of disease, etc."). Diseases, etc. that need to be reported to the Specified Authorized Regenerative Medicine Committee and the Minister of Health, Labour and Welfare should be reported according to "8.8. Reporting of diseases, etc. to the Specified Authorized Regenerative Medicine Committee and the Minister of Health, Labour and Welfare".

#### 8.3. Definition of Serious Adverse Event

A serious adverse event is defined as any of the following:

- 1) Death
- 2) Those that may lead to death
- 3) In need of hospitalization or prolonged hospitalization for treatment
- 4) Disability
- 5) Those that may lead to disability
- 6) Those that are as serious as those listed in 3) to 5) above.

#### 7) Congenital diseases or anomalies in later generations

Note that "hospitalization" in 3) does not include reexamination, hospitalization for follow-up or extended hospitalization, and hospitalization solely for the purpose of performing treatment or tests that were planned prior to the start of the study (e.g., scheduled surgery or tests) during the study. (However, any new occurrence during such hospitalization will be treated as an adverse event.)

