## 5. Study Method

### 5.1. Design

This is an open-label, single arm, Phase I study to evaluate the tolerability, safety, pharmacokinetics, pharmacodynamics, and antitumor effects of iPS-NKT cell in combination with auto-DC/Gal in patients with recurrent or advanced head and neck cancer who are refractory or intolerant to standard of therapy.

The dosing regimen involves both a submucosal injection of auto-DC/Gal at  $1.0 \times 10^8$  cells (fixed dose) followed by tumor-feeding arterial administration of the iPS-NKT cell at one of two dose levels: initial dose (first dose) cohort:  $3.0 \times 10^7$  cells/ $m^2$ , or second dose cohort:  $1.0 \times 10^8$  cells/ $m^2$ , administered at once, respectively. The iPS-NKT cell is administered at once five days after the DC/Gal injection. We avoid same-day administration of the investigational product to more than two subjects, and there must be a minimum interval of at least seven days before administering the investigational product to the following subject. We employed the three-by-three (3+3) design for dose escalation in this trial. Ultimately, the maximum tolerated dose (MTD) will be determined based on a total of six subjects with one or less DLT occurrences.

The screening period begins after obtaining the informed consent from each subjects. Based on the results of the screening tests, eligible subjects are registered in this study. One week prior to the start of study treatment, the subject's peripheral blood is collected, and auto-DC/Gal is manufactured (auto-DC/Gal preparation period).

DLT assessment period starts from the injection of auto-DC/Gal to 14 days after the iPS-NKT cell administration. During DLT assessment period, subjects will be carefully monitored under hospitalization. The PI or SI may leave the hospital at his/her own discretion only if the patient does not develop non-hematologic toxicity or hematologic toxicity of Grade 2 or higher and Grade 3 or higher on or after Day 7 of iPS-NKT cell administration, and be able to contact the study site and home doctor of the subjects, if any, in the event of an adverse event.

The Independent Data Monitoring Committee, consisting of members designated by the PI and study coordinating physicians, monitors the safety of the study and may make recommendations regarding the continuation of the study.

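### The note to serious-adverse-event item 3 excludes extended hospital stays without qualification, so an inpatient event whose only serious feature is a longer stay for treatment can be recorded as non-serious

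*Protocol*

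**What the plan says.** Item 3 of the protocol's serious-adverse-event definition (section 8.3) reads "In need of hospitalization or prolonged hospitalization for treatment". The note after the list says that hospitalization in item 3 "does not include reexamination, hospitalization for follow-up or extended hospitalization". It also leaves out "hospitalization solely for the purpose of performing treatment or tests that were planned prior to the start of the study" and closes by saying that "any new occurrence during such hospitalization will be treated as an adverse event".

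Section 5.1 states: "During DLT assessment period, subjects will be carefully monitored under hospitalization". Section 1.3.4 makes this a requirement in principle. Both sections allow a subject to leave from Day 7 after iPS-NKT if specified toxicity has not occurred.

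Four other places bear on the point:
- The second section numbered 8.3 (response to adverse events) names a longer hospital stay as a possible measure when specialist care is needed.
- Section 8.6.1, item 7, records every adverse event as serious or non-serious.
- The table in 8.8 requires a 15-day report for admission or prolonged hospitalization and has no exclusion like the one in the note.
- Section 13.1, item 1, lists information on serious adverse events among the grounds for stopping or suspending the study.

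**The concern.** An extended stay and a prolonged stay are the same thing, so the definition counts in one sentence what it removes in the next. In many trials this would be a small slip, because most events qualify through a new admission. Here subjects are in hospital by design while tolerability is judged. Someone already admitted cannot be newly admitted, so an event can meet item 3 only by lengthening the stay, and that is the limb the note appears to delete. The closing sentence of the note does not repair this: it makes a new occurrence an adverse event, not a serious one.

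At stake is whether two people coding the same event would give the same answer, and whether the serious-event information considered under 13.1 is complete.

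**Working it through.** No statistical figure is involved. The check sets the texts side by side, counts days and traces one record.

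**1. Two readings of the note.**
- *Literal:* the follow-up qualifier belongs only to the noun before it, and extended hospitalization stands alone. Any extension is then excluded, which contradicts item 3.
- *Narrow:* the qualifier covers both nouns, so only stays or extensions for re-examination or follow-up are excluded. This agrees with item 3, where treatment is the dividing line.

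The exclusion for pre-planned procedures carries an explicit limiter (solely). The term for extended stays carries none.

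**2. What the note reaches.** It names item 3 only, which has two limbs: admission and prolongation. Items 1, 2, 4, 5 and 7 are untouched, including "Those that may lead to death" and "Those that may lead to disability". Item 6, "Those that are as serious as those listed in 3) to 5) above", also stays open. It is a matter of judgement, however, and its benchmark includes item 3, which the note narrows.

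**3. When it applies.**
- Study calendar: DC/Gal on Day 1, iPS-NKT on Day 6.
- End of the DLT window: 6 + 14 = Day 20 (the calendar's last treatment column is Day 19, ±3 days).
- Earliest leave: Day 6 + 6 = 12 if the iPS-NKT day is counted as Day 1, or 6 + 7 = 13 if it is counted as Day 0.
- Remainder of the window after the earliest leave: 20 − 13 = 7 to 20 − 12 = 8 days.

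For about the last week, a subject who has left can still qualify by a new admission. A subject kept in because of toxicity cannot.

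**4. One illustrative record.** A Grade 2 non-haematological event, with no transfusion or G-CSF, starts on Day 12 in an inpatient. The stay is extended beyond Day 20 to treat it. No other serious feature is present.

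| Rule | Suspected related | Judged unrelated |
|---|---|---|
| Item 3 without the note | serious | serious |
| Item 3 with the note, literal | not serious under item 3 | not serious under item 3 |
| Item 3 with the note, narrow | serious | serious |
| 8.8 table | 15-day report | outside its scope |
| DLT (5.2) | no, below Grade 3 | no |

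Under the literal reading, a suspected-related event can be non-serious in the 8.6.1 field and yet reportable under 8.8. Section 8.2 limits 8.8 to illness suspected to be caused by the treatment, so an event judged unrelated has no such backstop.

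**5. Where seriousness is used.** DLT in 5.2 rests on CTCAE grade, transfusion or G-CSF use, and causality. The tables in 10.5.2.2 are by system organ class and preferred term, dose, severity, causality and CTCAE grade. Seriousness enters neither. It enters the 8.6.1 field and 13.1, item 1.

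**The case against.** The best defence is that the note cannot be read word by word. A re-examination is not itself a hospitalization, so the phrase must be shorthand for a stay, or its extension, for re-examination or follow-up. The rest of the note also concerns stays not caused by treating an event, and the 8.8 table keeps prolonged hospitalization. On that view nothing is lost. This reading is plausible and may be what was intended. It is not what the sentence says, though, and a definition that two coders can defensibly apply in opposite ways needs correcting even if the benign sense was meant.

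A second objection is that 8.3 and 8.8 differ in scope by design, since one ignores causality and the other requires suspicion of it. That is fair, and a difference in scope alone would be no defect. It does not explain why a suspected-related prolongation should be non-serious in one and on the serious-event timetable in the other.

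A reader might go further and infer that serious events in the DLT window will generally be coded non-serious, or that the tolerability result is biased. The documents do not support either. Six of the seven criteria are untouched and item 6 may catch some of the remainder. Hospitalization is required only in principle, with conditional leave. The DLT endpoint does not use seriousness, and no serious-event rate is among the analyses the protocol names. The event would still be reported, graded and tabulated, and the monitoring committee reviews all adverse events. Nor does the length of the inpatient window measure how many events would be misclassified.

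**Conclusion.** The point holds as a contradiction in the definition, with possible but not certain under-classification. Read literally, the note conflicts with item 3 and with the 8.8 table. The events exposed are those whose only serious feature is a longer stay for treatment, in subjects still in hospital. If suspected related, they are still reported under 8.8; if judged unrelated, they are not.

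The effect is confined to the seriousness field and to the serious-event information behind 13.1, item 1. Its size cannot be stated as a rate, because the protocol gives no expected frequency of such events. The conclusion assumes that the note is applied as worded and that item 6 is not used to bring the event back in.

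**What to change.** Reconcile item 3, its note and the 8.8 table. Reword the note along these lines: *hospitalization, or its extension, solely for re-examination, follow-up observation, or treatment or tests planned before the study is not counted; prolongation needed to treat an adverse event, including prolongation of the protocol-required stay, meets item 3.* Use the same rule in the case report form guidance for the seriousness field in 8.6.1, item 7.

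The cost is one sentence in the protocol and the matching guidance. A few more events may be coded serious, and any event already recorded with an extended stay should be checked against the new wording. No endpoint, sample size or analysis changes.

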### 8.3. Response to Subjects in the occurrence of the Adverse Events or Quality Defects

When an adverse event or quality defect is observed, the PI or SI will immediately take appropriate measures and inform the subject if the administration of DC/Gal or iPS-NKT cells is discontinued or if treatment for the adverse event should be taken. If an adverse event or symptom is recognized by the PI or SI as requiring more specialized consultation, the PI or SI will promptly collaborate with an appropriate specialist and can take measures including extension of the hospitalization period, if necessary.

If an adverse event with an undeniable causal relationship to DC/Gal or iPS-NKT cells has not yet recovered at the time of completion or discontinuation of the study, observation should be continued as much as possible until recovery or attenuation of symptoms, in principle. However, this does not apply when the PI or SI determines that the influence of the study have disappeared, the subject's safety is sufficiently ensured, and further follow-up is not necessary.

### 8.4. Reportable Adverse Events and Quality Defects

- 1) All adverse events occurring from the date of consent to the last day of the observation period (at the time of discontinuation) should be reported regardless of whether or not they are causally related to DC/Gal or iPS-NKT cells, and the patients should be observed until they recover from the adverse events or the last day of the observation period (at the time of discontinuation). All adverse events judged to be causally related to DC/Gal or iPS-NKT cells should be reported until the end of the study period.
- 2) All information on quality defects occurring during the study period shall be reported.

### 8.5. Reporting Procedures for Adverse Events and Quality Defects

All adverse events and quality defects occurring during the above period shall be documented by the PI or SI without discrepancy in the medical record and case report form.

## 8.6. Description required for evaluation of adverse events and quality defects

### 8.6.1. Adverse event

1) Description of the adverse event

Generally, the name of the adverse event should be recorded by the name of the diagnosis and the name of the disease (illness). If the name of the diagnosis or disease cannot be identified, or if it is deemed appropriate not to use the name of the diagnosis or disease by the PI or SI, the clinical symptoms or signs should be used as the name of the adverse event.

2) The date of occurrence

3) The date of outcome

4) Outcome: recovery, mild recovery, recovered but with sequelae, not recovered, death, unknown

5) Measurement (administration of DC/Gal or iPS-NKT cell): no change, discontinue, pending, not applicable

6) Other response: none, drug therapy, others

7) Seriousness: Non-serious, serious

8) Severity: Severity is judged based on CTCAEv5.0 JCOG version.

9) Causal relationship with DC/Gal or iPS-NKT cells: No relation, relation cannot be ruled out

### 8.6.2. Quality defects

1) The type of quality defect

2) The date the quality defect is confirmed

3) The date of the incident

4) Serial number of DC/Gal or iPS-NKT cells in which quality defects occurred

5) Possible causes and the circumstance of quality defects

6) Measures against quality defects

7) Whether there are any adverse events due to the quality defects

① Yes: type of the adverse event

② No: Possibility of the occurrence of severe adverse event

### 8.6.3. Causal relationship between adverse events and DC/Gal or iPS-NKT cells, and recoverability of adverse events

Recovery from an adverse event is defined as the absence of the adverse event or restoration to the state prior to administration. The causal relationship between the adverse event and DC/Gal or iPS-NKT cells should be determined by taking into consideration the subject's general condition, complications, concomitant

medications/adjunctive therapies, and time-related factors.

No causal relationship:

when there is a stronger indication that the adverse event is due to other causes other than those listed below or other causes.

A causal relationship cannot be ruled out:

A temporal relationship is observed between the administration of DC/Gal or iPS-NKT cells and the onset of the event, and the event attenuates with time after the discontinuation of DC/Gal or iPS-NKT cells, but recurs or worsens with subsequent re-administration, or no obvious confounding risk factors such as the subject's general condition, complications, concomitant medications, or concomitant therapies.

#### 8.7. Measures to be taken in case of outbreak of disease, etc.

- 1) When investigators become aware of an outbreak of disease suspected to be caused by DC/Gal or iPS-NKT cells, he/she shall promptly report it to the PI and the study coordinating physician.
- 2) The PI shall report to the hospital director using Appendix Form-C (hospital form).
- 3) The hospital director or the study coordinating physician shall instruct the PI to take necessary measures such as discontinuation of the regenerative medicine, etc.
- 4) The hospital director or the PI shall promptly notify the specified cell-processing manufacturer (Chiba University Hospital Center for Advanced Medicine and RIKEN) that produced the DC/Gal and iPS-NKT cells of the occurrence of the situation and the measures taken.

#### 8.8. Reporting of disease, etc. to the Specified Authorized Regenerative Medicine Committee and the Minister of Health, Labour, and Welfare

- 1) When a hospital director becomes aware of any of the following diseases, etc., he/she shall report it to the Specified Authorized Regenerative Medicine Committee and the Minister of Health, Labour and Welfare in accordance with Table 1.
- 2) Report to the Specified Authorized Regenerative Medicine Committee using Appendix Form 1 of "Report on Diseases, etc." (related to Article 35 of the Ministerial Ordinance). Reports shall also be submitted to the Minister of Health, Labour and Welfare through jRCT.

Table 1

| Severity of disease etc.                                                                                                                                                                                                                               | Entity to be reported                                                                                            | Deadline                                                                                                                                                                                                                      |
|--------------------------------------------------------------------------------------------------------------------------------------------------------------------------------------------------------------------------------------------------------|------------------------------------------------------------------------------------------------------------------|-------------------------------------------------------------------------------------------------------------------------------------------------------------------------------------------------------------------------------|
| ① Death
② Case that may lead to death                                                                                                                                                                                                               | The Specified Authorized
Regenerative Medicine
Committee
The Minister of Health,
Labour, and Welfare | Within 7 days                                                                                                                                                                                                                 |
| ① Cases requiring admission to a medical
institution for treatment or prolonged
hospitalization
② Disability
③ Cases that may lead to disability
④ Cases that are serious
⑤ Congenital disease or abnormality in later
generation | The Specified Authorized
Regenerative Medicine
Committee
The minister of health,
labour, and welfare | Within 15 days                                                                                                                                                                                                                |
| ① Occurrence of disease, etc. due to an
infectious disease that is suspected to be
caused by the provision of regenerative
medicine, etc.                                                                                                     | The Specified Authorized
Regenerative Medicine
Committee                                                   | Every 60 days from the
date of submission of
the plan for providing
regenerative medicine
to the Minister of
Health, Labour and
Welfare, and within 10
days after the expiration
of designated period |

